## Abstract

**Background:**

Currently, the treatment of anemia in preterm infants is based on packed red blood cell (RBC) transfusions from adult donors. Oxygen (O2) is mainly transported to the tissues bound to hemoglobin (Hb). In extremely low gestational age neonates (ELGANs), fetal hemoglobin (HbF), which has a higher affinity for O2, represents up to 95% of circulating hemoglobin. During the first month of life, the majority of ELGANs will require an adult-donor RBC transfusion causing HbF levels to rapidly drop. HbA releases 50% more oxygen in peripheral tissues than HbF. Increased release of O2 in the retina is one of the main factors related to the development of retinopathy of prematurity (ROP). Collecting umbilical cord blood and using autologous umbilical cord whole blood (UCB) transfusions would contribute to maintaining physiological HbF concentrations in newborns and avoid oxygen-in-excess derived damage.

**Methods:**

This is a randomized, double-blinded, multicenter clinical trial. ELGANs ≤28 weeks of gestational age will be randomized 1:1 to receive an autologous umbilical cord blood transfusion (intervention arm) or standard transfusion of packed RBC from an adult donor (control arm) to assess ROP development. Assuming a 50% reduction in ROP incidence, 134 patients (67 per group) will be recruited. When blood transfusion is indicated, the Blook Bank will supply UCB or RCB according to the patient's group. The primary endpoint is the incidence of any ROP. Secondary endpoints are assessessment of treatment safety, results of biomarkers related to ROP and its chronology, and urine oxidative stress markers. In addition, the cellular composition of umbilical cord blood and its relationship with prematurity-related pathologies will be analyzed. All patients will be followed-up to 24 months of corrected age to evaluate their neurodevelopment.

**Discussion:**

ROP is a major cause of irreversible blindness in preterm newborns. Transfusions with adult donor blood can lead to complications, including ROP. UCB transfusions offer advantages by maintaining physiological HbF levels and potentially optimizing postnatal development. Moreover, autologous UCB transfusion could reduce risks associated with heterologous blood products, although volume collection remains challenging. UCB contains growth factors and progenitor cells that may impact ROP.

## Introduction

Retinopathy of prematurity (ROP) is a common comorbidity associated with extreme prematurity that affects up to 64% of extremely low gestational age neonates (ELGANs) below 28 weeks of gestational age (GA) (1, 2). ROP is a condition exclusive to preterm newborns and is the leading cause of blindness in ELGANs with significant neurodevelopmental implications in the short and long term (3).

Physiologic retinal development requires a relative hypoxemic microenvironment during intrauterine growth, where the arterial partial pressure of oxygen (PaO2) ranges from 30 to 40 mmHg. However, PaO2 rapidly increases to 100 mmHg whithin minutes after premature birth, hindering retinal blood vessel growth. In the first stage of ROP, hyperoxia suppresses the production of vascular endothelial growth factor (VEGF) and erythropoietin (EPO), leading to retinal vasoconstriction and localized hypoxia, ultimately causing delayed retinal development. Additionally, preterm birth causes the depletion of factors such as insulin-like growth factor 1 (IGF-1), which seems to contribute to the alteration of retinal vascular development (4, 5). In the second stage, the prolonged retinal hypoxia triggers the production of proangiogenic factors, leading to pathological and aberrant neovascularization that leads to the formation of fibrous scars and may potentially result in retinal detachment and subsequent risk of blindness or severe loss of visual acuity.

The severity of ROP inversely correlates with the degree of prematurity (6). Prematurity creates a favorable environment for this condition by exposing the immature retina to high oxygen levels. Despite extensive research conducted over the past six decades to investigate the relationship between prematurity, oxygen, and ROP, the treatment strategies for ROP are focused on applying therapies once the pathology has been developed such as laser therapies or intravitreal injection of bevacizumab (7, 8). However, no effective strategy has been found to significantly prevent the progression of ROP before its onset. Limited supplemental oxygen has been evaluated as a potential intervention, but this practice has the counterpart of increasing mortality (9, 10).

Red blood cell (RBC) transfusions have been associated with a higher incidence of ROP, and its severity is directly related to the volume of blood transfused (11). In term newborns, fetal hemoglobin makes up about 60%–80% of total hemoglobin. In ELGANS, fetal hemoglobin makes up 90%–95% of total hemoglobin (12). Although the physio-pathological mechanism is unknown, it is postulated to be linked to the significant increase in adult hemoglobin (HbA) levels. HbA releases up to 50% more oxygen than fetal hemoglobin (HbF) to peripheral tissues. Because blood from bank donors comes exclusively from adults, RBC transfusions increase HbA levels generating a hyperoxic stimulus in the retinal capillaries that could trigger the development of ROP (13–15). Moreover, low HbF levels have also been associated with ROP (16, 17). Additionally, recent studies have suggested that HbF could protect against oxidative stress due to its biochemical properties (18, 19).

Based on these premises, the utilization of umbilical cord blood transfusion (UCB) from healthy newborns has been proposed to prevent ROP in preterm infants (6). This approach is feasible and safe, although it is not exempted from the inherent risks associated with allogeneic transfusions (20). As an alternative, autologous UCB transfusion is suggested for treating anemia in ELGANs. Autologous UCB transfusions (UCBa) have been widely employed in full-term infants with congenital heart diseases requiring extracorporeal surgery (21, 22). The safety of UCBa has been extensively demonstrated, with no adverse effects reported in numerous studies involving over a hundred transfused patients (23–26). Furthermore, the transfusion risks associated with using allogeneic blood are eliminated in this approach. In premature patients, less information is available. However, most studies have shown that a volume ranging from 20 to 25 ml/kg is usually collected, meeting the requirements for at least one to two autologous transfusions (24, 25). Not only has UCBa been seen as equivalent to adult-donor RBC in increasing hematocrit (24), but this approach could also sustain HbF levels during the critical period of extremely preterm infants’ development. Additionally, UCB is enriched with self-hematopoietic growth factors, hematopoietic stem cells, and mesenchymal stem cells, which play a crucial role in developing connective tissue and blood vessels (27). Some authors have hypothesized that these cells could modulate angiogenesis and promote an appropriate retinal microenvironment, potentially reducing the progression of ROP (27–29).

We hypothesize that using UCBa in the first weeks after birth will contribute to keeping elevated HbF blood concentrations and subsequently reduce the risks inherent to HbA of interfering with the growth of the retinal vascular system.

This study aims to assess the effect of UCBa transfusion vs. standard treatment with packed adult-donor RBC in the incidence of ROP. Secondary objectives are to determine the impact of UCB autologous transfusion on the expression of biochemical markers of ROP, to determine the effect of UCB autologous transfusion on oxidative stress, to characterize the specific composition of stem cells in UCB in preterm newborns and its relationship with complications of prematurity.

## Methods and analysis

### Study design

To test the hypothesis, we have designed a randomized, multicenter, double-blinded trial to evaluate the effect of UCBa transfusion on the development of ROP compared to transfusion of adult-donor RBC in preterm infants with GA ≤28 weeks. Patients will be randomized in a 1:1 ratio to receive either UCBa transfusion or standard treatment with adult-donor RBC.

The study will be conducted at three hospitals: The University and Polytechnic Hospital La Fe (Valencia, Spain), the University Clinical Hospital of Santiago (Santiago, Spain), and the Maternal and Child University Hospital Complex of Las Palmas (Las Palmas, Spain). The protocol was written following the Standard Protocol Items: Recommendations for Interventional Trials (SPIRIT) guidelines. The study was registered at European Union Drug Regulating Authorities Clinical Trials Database (EudraCT) with the identifier number 2022-003821-22. Figure 1 shows the SPIRIT flow diagram of the study.

**Figure 1 F1:**
[figure not shown]
Flow chart illustrating intervention and control arm according to clinical trial protocol.

### Study population

Inclusion criteria: Preterm infants with GA ≤28 + 6 weeks of GA.

Exclusion criteria are one or more of the following: major congenital malformations, monochorionic twin pregnancy, chromosomal abnormalities, hemoglobinopathies, isoimmunization, critical condition at birth with a predicted fatal outcome, and refusal to participate and sign the informed consent.

Patients will be managed according to the usual protocols regarding oxygenation limits. The enrolled patients’ targeted oxygen saturation range will be 91%–95%. Transfusion thresholds will be carried out according to local guidelines.

### Intervention

Patients will be randomized to receive either whole UCBa, intervention group, or standard adult-donor packed RBC, control group. For patients with anemia requiring blood transfusion according to the Spanish Society of Neonatology's standards Committee threshold's recommendations (30), the responsible physician will make the corresponding request for transfusion indicating the volume needed. The Blook Bank will supply UCBa or RBC according to the patient's group, but bag labeling will be indistinguishable. In case there is not enough UCBa, RBC will be administered. As the maximum storage of UCB is 35 days, both groups will receive adult-donor RBC concentrates after this age. Transfusion's traceability will always be maintained through the e-Delphyn Transfusion Service software. UCB extraction and storage protocols are detailed in Appendix I.

### Primary outcome

The primary outcome is the incidence of ROP in both groups. Diagnosis and staging of ROP will be established according to “International Classification of the Retinopathy of Prematurity, Third Edition (ICROP3)”. ROP diagnosis will be made by an expert ophthalmologist using indirect ophthalmoscopy and RetCam imaging.

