### Secondary outcomes

Outcomes related to effectiveness
-Recovery of hematocrit and hemoglobin values.-Transfusion requirements during admission (number and volume of transfusions received).-Treatment with EPO and other adjuvant treatments for anemia such as iron and folic acid supplementation (time of initiation, number of doses received).-Assessment of post-transfusion tissue oxygen transfer status: Brain and somatic NIRS value, oxygen saturation measured by pulse oximetry, lactate, HbF levels.Outcomes related to safety
-Incidence of acute transfusion reactions.-Incidence of late complications: bronchopulmonary dysplasia, periventricular leukomalacia, necrotizing enterocolitis, hemodynamically significant patent ductus arteriosus, sepsis, and death.Outcomes related to retinopathy markers
-Serum levels of EPO, VEGF and IGF-1.-HbF levels.Outcomes related to ROP treatment
-ROP severity-Laser therapy-Anti-VEGF administrationOutcomes related to UCB cellularity and oxidative stress.
-Quantification of reactive oxygen species in urine.-Composition of stem cells in UCB.

Data concerning retinopathy and oxidative stress biomarkers quantification and stem cells typification is provided in Appendix II.

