### Sample size calculation and power

We consider the development of ROP a competitive outcome with mortality due to its late onset during postnatal development. The combined variable death or ROP was considered the primary study variable. The incidence of death or ROP in our center in ≤28 weeks is 41%. A 50% reduction in the incidence will be considered clinically significant, so considering a significance level of 0.05 and a power of 0.8, the calculated sample size is 122 patients. Assuming a drop ratio of 10%, 134 patients will be recruited for the study (67 in each group).

University and Polytechnic Hospital La Fe is a tertiary center with 6,000–6,500 births annually. In addition, two other recruiting centers, University Clinical Hospital of Santiago (2,000–2,200 births annually) and Maternal and Child University Hospital Complex of Las Palmas (4,500–4,800 births annually), are included in the study, so we estimate that the sample size could be accomplished in the three years of the study duration.

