### Statistical analysis

The following sets of analyses are planned: (1) All included patients, regardless of whether they were transfused or not; (2) All included patients who received transfusions, as per intention-to-treat (including intervention group patients who received adult donor blood transfusions due to unavailability of umbilical cord blood); (3) All included patients who received transfusions as per protocol (excluding intervention group patients who received adult donor blood transfusions). Secondary analyses will also examine the effect of the two treatment strategies on the described secondary variables. An interim analysis of the results will be conducted once half of the sample has been collected to assess the presence of any relevant safety or mortality outcomes. An external committee will be proposed to perform the calculations while maintaining blinding until evaluation.

Categorical variables are described with each category's numerical count (percentage). If the application assumptions are met, they are compared with Pearson's chi-square test, and if not, Fisher's exact test. Continuous variables are represented with Tuckey box plots. If the constant variables are standard (*p* > 0.05 in the Shapiro–Wilk test), they are described with the mean ± standard deviation. They are compared using Student's *t*-test, first testing the hypothesis of equality of variances using Levene's test. If abnormal, they are described with a median (p25, p75) and compared with the nonparametric Mann–Whitney *U*-test. Comparison between both groups of repeated measures over time is performed by a two-way analysis of variance (ANOVA) test, first testing Mauchly's sphericity hypothesis and rejecting it with *p* < 0.05. Survival times are expressed with their median [95% confidence interval (95% CI)], and between-group comparison is performed with the log-rank test. Throughout the study, a *p* < 0.05 is accepted as the limit of statistical significance. The magnitude of the effect is quantified with the risk difference (expressed as a percentage), and its precision is indicated with the 95% CI.

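### Two primary endpoints are stated, ROP alone and death or ROP, and the sample size fits only the composite

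*Protocol article*

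**What the plan says.** All of this is current text in the protocol article.

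- Abstract, Methods: "The primary endpoint is the incidence of any ROP". The same paragraph attaches the 50% reduction, and the 134 patients, to ROP incidence.
- Primary outcome: "The primary outcome is the incidence of ROP in both groups", diagnosed and staged by ICROP3.
- Secondary outcomes, safety list: it closes with "hemodynamically significant patent ductus arteriosus, sepsis, and death", so death is secondary.
- Sample size calculation and power: "We consider the development of ROP a competitive outcome with mortality due to its late onset during postnatal development". Then: "The combined variable death or ROP was considered the primary study variable". The control rate is a composite rate: "The incidence of death or ROP in our center in ≤28 weeks is 41" (per cent). The effect follows: "A 50% reduction in the incidence will be considered clinically significant". With significance level 0.05 and power 0.8 the section reaches 122 patients, and 134 after 10% dropout.
- Statistical analysis: the first analysis set is "All included patients, regardless of whether they were transfused or not". Categorical variables are compared by chi-square or Fisher's exact test, with a risk difference. The section does not say which of the two primaries is tested.

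**The concern.** The outcome section cannot be read as shorthand for the composite, because death has its own place among the secondary outcomes. An analysis plan that named one endpoint would still contradict one part of this article.

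The sample-size section itself explains why the choice matters: many of these infants may die before ROP can appear. With ROP alone as primary, those deaths are not events, and there are two ways to handle them. If they are counted ROP-free, excess deaths in one arm lower that arm's apparent ROP rate. If they are dropped, the comparison is conditional on survival and a mortality difference disappears from the primary result. In addition, the 41% and the 122 cannot be carried over to ROP alone.

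**Working it through.** **1. Which endpoint produces 122?** The inputs from the sample-size section are p1 = 0.41, p2 = 0.205, alpha 0.05 (sidedness not stated) and power 0.80. The pooled formula per arm is n = [z_α√(2p̄(1−p̄)) + z_β√(p1(1−p1) + p2(1−p2))]² / (p1−p2)², with p̄ = 0.3075.

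- One-sided: (1.645 × 0.6526 + 0.842 × 0.6363)² / 0.042025 = 61.6, so 62 per arm, 124 in total. The unpooled version gives 59.6, so 60 per arm, 120 in total. The stated 122 lies between them.
- Two-sided: 79 per arm, 158 in total.
- Dropout: 122 × 1.1 = 134.2, the stated 134.

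The stated number is therefore reproduced from the composite rate, and only with a one-sided test.

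**2. What would ROP alone need?** No ROP-only rate for the centre is given. Assumption: death without ROP makes up 5, 10, 15 or 20 of the 41 points, leaving ROP at 36, 31, 26 or 21% of all infants. Power is the exact binomial probability that the Pearson chi-square test rejects with 61 per arm. Total N is from the pooled formula, before dropout.

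| Control → halved | Power, two-sided | Power, one-sided | N, two-sided | N, one-sided |
|---|---|---|---|---|
| Composite 41 → 20.5% | 0.70 | 0.80 | 158 | 124 |
| ROP 36 → 18% | 0.62 | 0.74 | 190 | 150 |
| ROP 31 → 15.5% | 0.54 | 0.66 | 232 | 182 |
| ROP 26 → 13% | 0.45 | 0.58 | 290 | 228 |
| ROP 21 → 10.5% | 0.35 | 0.48 | 376 | 296 |

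From the unrounded values, the switch from composite to ROP alone costs about 7 to 35 points of power two-sided and 6 to 32 one-sided.

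**3. How do deaths enter?** Illustration with assumed rates: ROP in survivors 34% in both arms, deaths 10% in control and 15% in the cord-blood arm.

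- Deaths counted ROP-free: 0.90 × 0.34 = 30.6% against 0.85 × 0.34 = 28.9%, an apparent benefit of 1.7 points.
- Deaths dropped: 34% against 34%, no difference.
- Composite: 0.10 + 0.306 = 40.6% against 0.15 + 0.289 = 43.9%, a harm of 3.3 points.

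Only the composite shows the mortality difference.

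**The case against.** Four stronger readings are tempting, and the article does not support them.

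- *An early death counts as a non-case.* No section says so. Using all included patients as the denominator suggests it, but dropping such infants is equally compatible with the text, and the rule could stand in an analysis plan that is not shown. What does stand is that under either rule death is not an event.
- *The sign of the effect reverses.* It does so only if deaths are counted ROP-free. The rates in the illustration are assumed, and with 67 per arm the differences of 1.7 and 3.3 points have standard errors of about 8 and 8.5 points. The example shows a direction of bias, not its likely size.
- *Power falls from 0.80 to as little as 0.35.* This mixes a one-sided baseline with a two-sided result. Two-sided, the composite itself has only 0.70, which is a separate matter of sidedness. The low end also needs death without ROP to be about half of the 41%, which nothing in the article supports.
- *The endpoint could be picked after unblinding.* Two stated primaries leave that open, but an unseen analysis plan may already fix the choice.

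It can also be argued that ROP alone is what was meant, since the study aim, the abstract and the outcome section all speak of ROP. That is a fair reading, but it leaves the sample size without a basis. The introduction's figure of up to 64% ROP below 28 weeks cannot fill the gap: in the same infants, ROP alone cannot exceed the 41% for death or ROP.

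**Conclusion.** The point stands and must be fixed: the article names two incompatible primary endpoints, and its rate, effect and sample size belong to the composite. This conclusion rests on the text alone.

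The size of the power loss is conditional. It rests on the assumed split of the 41%, on ROP being taken over all 61 infants per arm, and on a 50% relative reduction in whichever endpoint is tested. The last condition also limits the composite, because halving it requires deaths to fall too. If only ROP were halved, the composite would move from 41% to between 23 and 30.5% over the same range of splits, and its two-sided power at 61 per arm would be about 0.57 to 0.23 (normal approximation). The case for the composite is therefore consistency and proper handling of death, not a guarantee of power.

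**What to change.** Name one primary endpoint, in the same words, in the abstract, Primary outcome, Sample size calculation and power, and Statistical analysis.

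- **Option that matches the stated rationale and sample size:** change the abstract and the outcome section to death before completed ROP ascertainment, or any ROP by ICROP3, in all randomised infants. Report ROP and death separately as well, so that they are read together. Tie completed ascertainment to the end of ROP screening. The 40-week visit in the Follow-up section lists no eye examination and does not define it. Attach the abstract's 50% reduction to the composite.
- **If ROP alone is kept:** give a ROP-only control rate, restate the power or the sample size, and fix how infants who die before diagnosis are classified.

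The first option is mainly a wording change, since ROP and death are already among the outcomes. The second may mean a larger trial: on the assumed splits, 190 to 376 infants two-sided or 150 to 296 one-sided, before dropout. Either way the sidedness of the test should be stated. Whether the registry entry also needs changing cannot be judged from the article.

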### Secondary outcomes

Outcomes related to effectiveness
-Recovery of hematocrit and hemoglobin values.-Transfusion requirements during admission (number and volume of transfusions received).-Treatment with EPO and other adjuvant treatments for anemia such as iron and folic acid supplementation (time of initiation, number of doses received).-Assessment of post-transfusion tissue oxygen transfer status: Brain and somatic NIRS value, oxygen saturation measured by pulse oximetry, lactate, HbF levels.Outcomes related to safety
-Incidence of acute transfusion reactions.-Incidence of late complications: bronchopulmonary dysplasia, periventricular leukomalacia, necrotizing enterocolitis, hemodynamically significant patent ductus arteriosus, sepsis, and death.Outcomes related to retinopathy markers
-Serum levels of EPO, VEGF and IGF-1.-HbF levels.Outcomes related to ROP treatment
-ROP severity-Laser therapy-Anti-VEGF administrationOutcomes related to UCB cellularity and oxidative stress.
-Quantification of reactive oxygen species in urine.-Composition of stem cells in UCB.

Data concerning retinopathy and oxidative stress biomarkers quantification and stem cells typification is provided in Appendix II.

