The limitations of this study are inherent to a clinical trial and are mainly manifested in two aspects. Firstly, the difficulty of recruiting patients in the complex environment of Neonatal Intensive Care Units at the birth of a preterm patient, where uncertainty about potential complications of this condition and other concurrent factors makes it challenging to approach the parents of eligible patients. For this reason, a multicenter design has been implemented, including three clinical units with sufficient annual admissions. On the other hand, there might be cases where the volume of blood collected needs to meet the complete transfusion needs of the patient. It is assumed that the most significant benefit of autologous transfusion will occur within the first two weeks of life due to the pathophysiology of the disease, during which time transfusion needs will be met. However, allogeneic transfusions are usually required as a supplement to meet complete requirements. This hypothesis is reinforced by the results presented by Hellstrom et al. (18), who found that only the drop in HbF during the first week of life was related to ROP. Moreover, the statistical analysis is designed in analysis sets to assess the actual impact of this effect. On the other hand, improving the collection technique and experience could help improve these results. Our group is working on developing an optimized system for cord blood collection.

The relevance of the trial is based on the need to address ROP, a serious ocular complication that currently lacks an effective treatment. Clinical trials like the one presented can be the beginning of a paradigm shift in transfusion medicine, using neonatal blood for neonatal patients whose situation differs significantly from adult patients, thereby improving the quality of care and clinical outcomes in this patient population.

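### The transfusion-linked secondary outcomes name no occasion, and the stated tests do not suit several unequally timed readings per infant; one value per infant would be valid but goes unadjusted for the pre-transfusion value.

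*Protocol article*

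**What the plan says.** The Secondary outcomes section of the protocol article lists two sets of transfusion-linked measurements under effectiveness: "Recovery of hematocrit and hemoglobin values", and "Assessment of post-transfusion tissue oxygen transfer status: Brain and somatic NIRS value", the latter together with pulse-oximetry saturation, lactate and HbF. Neither entry names the transfusion, the interval after it, or the number of readings per infant.

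Other sections show that transfusions will vary between infants:

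- The Introduction expects the collected cord blood to be enough for one or two transfusions: "meeting the requirements for at least one to two autologous transfusions".
- The Discussion says that "allogeneic transfusions are usually required as a supplement to meet complete requirements".
- Under Intervention, transfusion is given when an anemia threshold is met, not on a calendar. An infant in the cord-blood arm receives adult red cells when cord blood runs short, and both arms receive adult red cells after day 35.
- The number and volume of transfusions are themselves secondary outcomes.

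The Statistical analysis section assigns continuous variables to Student's t-test or the Mann-Whitney test. For repeated data it says: "Comparison between both groups of repeated measures over time is performed by a two-way analysis of variance (ANOVA) test", preceded by Mauchly's test of sphericity. It names no method for clustered readings and no covariate.

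**The concern.** A t-test or Mann-Whitney test assumes independent values. A repeated-measures ANOVA checked with Mauchly's test assumes the same occasions in every infant, with complete data. Readings tied to transfusions have neither property once an infant contributes more than one: they are correlated within the infant and unequal in number and timing.

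Analysts would then have two poor routes. Pooling the readings makes the standard error too small. Lining them up by transfusion order keeps only infants who needed that many transfusions, and that need arises after randomisation and may depend on the product received. A third route, one value per infant, is sound, but the text does not choose it.

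A separate and smaller matter is precision. For hemoglobin and hematocrit, a pre-transfusion value should be on record whenever a threshold is applied, yet no stated test adjusts for it.

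At stake is the evidence on whether cord blood corrects anemia as well as adult red cells do and changes oxygen transfer to the tissues. If the occasion is left open until the blind is broken at the last patient's hospital discharge, it could be chosen with the results in view.

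**Working it through.** The plan gives no figure to reproduce here, so the check sizes what each route would do.

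**Inputs.** Arm size is 61, half of the 122 in the sample size section. The significance level is 0.05, from Statistical analysis, taken as two-sided. The article gives neither transfusion counts nor within-infant correlation. Assumed: the number of transfusions per transfused infant is k = 1 + Poisson(2), mean 3, and the within-infant correlation (ICC) is 0.1 to 0.7.

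**Route 1: all readings pooled in a t-test.**

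- With a fixed number m per infant, the design effect is DE = 1 + (m − 1) × ICC, and the actual error rate is 2 × [1 − Φ(1.96/√DE)].
- For m = 3, DE = 1.2, 1.6, 2.0 and 2.4 at ICC 0.1, 0.3, 0.5 and 0.7. The error rates are 0.074, 0.121, 0.166 and 0.206.
- With varying k, m is replaced by E(k²)/E(k). Here E(k²) = 2 + 3² = 11, so 11/3 = 3.67 and DE = 1 + 2.67 × ICC = 1.27, 1.80, 2.33 and 2.87. The error rates are 0.082, 0.144, 0.200 and 0.247.
- A simulation under no arm difference (4,000 trials per setting) agrees:

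| ICC | All readings pooled | Per-infant mean | First transfusion only |
|---|---|---|---|
| 0.1 | 0.081 | 0.045 | 0.044 |
| 0.3 | 0.152 | 0.055 | 0.049 |
| 0.5 | 0.209 | 0.051 | 0.050 |
| 0.7 | 0.246 | 0.054 | 0.049 |

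**Route 2: ANOVA on a common number of occasions.** The share of transfused infants with at least J transfusions is P(Poisson(2) ≥ J − 1).

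- J = 2: 1 − e⁻² = 86%.
- J = 3: 1 − 3e⁻² = 59%.
- J = 4: 1 − 5e⁻² = 32%.
- With J = 3 and a mean of 2 or 4 transfusions, the share is 1 − 2e⁻¹ = 26% or 1 − 4e⁻³ = 80%.

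**Route 3: one value per infant.** The last two columns of the table stay at 0.044 to 0.055, so the stated t-test holds its level. What it gives up is precision. ANCOVA on the pre-transfusion value leaves a fraction 1 − ρ² of the variance of the post-transfusion value, where ρ is the pre/post correlation (assumed):

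- ρ = 0.3: 0.91, a cut of 9%.
- ρ = 0.5: 0.75, a cut of 25%.
- ρ = 0.7: 0.51, a cut of 49%.

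**The case against.** The strongest reply is that the article never says readings are taken after every transfusion, and never says they will be pooled. A reader might infer both from the word post-transfusion and the expectation of several transfusions, and conclude that the p-values will be too small. The text does not support that. It leaves the occasion open, and one value per infant fits the stated t-test.

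The ANOVA sentence is likewise not assigned to these outcomes. It may be meant for the biomarkers in Appendix II, which have fixed sampling times: weekly for VEGF over six weeks, and the first, 21st and 35th day for EPO and IGF-1. Nor do the figures show that an ANOVA would describe only the sickest infants: at means of 3 and 4 transfusions, 59% and 80% would remain.

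A reader might also think that leaving out the pre-transfusion value produces false positives. It does not; it costs precision. Nor is it certain that the value is left out, since recovery may mean change from before transfusion, and a two-way ANOVA could use before and after as its time factor.

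Finally, the unit of analysis may be set in a full protocol or analysis plan that is not shown.

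These replies stand as limits: any harm is conditional, and silence on the occasion would not by itself be a finding. What remains is that the article does prescribe tests, and none of them handles clustered, unequal readings or adjusts for a covariate.

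**Conclusion.** The point holds in a limited form. The stated tests do not suit these outcomes if more than one reading per infant is used. Under the assumed mean of three transfusions, pooling would raise the error rate from 5% to about 8% to 25%, and requiring three occasions would keep about 59% of transfused infants. With one value per infant the stated t-test is valid, and the remaining loss is the 9% to 49% cut in residual variance that ANCOVA would bring.

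All these figures rest on assumed counts and correlations. Only secondary outcomes are concerned, so the primary conclusion on retinopathy is not affected. The change is worth making because it is cheap and removes a choice that could otherwise follow the data.

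**What to change.** In the Statistical analysis section, state for these outcomes:

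1. The analysed occasion is each infant's first transfusion up to day 35, with one value per infant, compared by allocated arm.
2. The comparison uses ANCOVA adjusted for the value just before that transfusion. Hemoglobin and hematocrit should already be on record; near-infrared spectroscopy (NIRS) and lactate values are used where the infant is already monitored.
3. All transfusions enter only a supportive mixed model with a random infant intercept and the pre-transfusion value as covariate. It is supportive only because, from the second transfusion on, the pre-transfusion value may itself reflect the product already given.
4. The comparison is limited to transfused infants. This is a milder selection than one by transfusion count: before the first transfusion no allocated product has been given and treating staff are blinded, so need for it should not depend on arm.

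The cost is a few sentences of analysis text, plus noting NIRS and lactate values just before transfusion where they are available. Fewer transfusions enter the main comparison, and some pre-transfusion NIRS and lactate values may be missing, so the text should also say how those infants are handled.
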